## Background

Intermittent catheterization (IC) is a widely used and clinically effective method for managing non-obstructive rinary retention and neurogenic bladder, particularly in individuals with spinal cord injuries, multiple sclerosis, and other neurological conditions [[1], [2], [3]]avoiding upper urinary tract complications and improving urinary symptoms, and quality of life [4,5]. However, despite its benefits, adherence to IC remains a significant challenge. Many patients struggle with psychological discomfort, procedural difficulties, and inadequate training, all of which can negatively impact their acceptance and consistent use of IC [6,7].

Educational interventions play a critical role in addressing these barriers and improving adherence to IC [4]. Existing studies highlight the importance of providing structured training to help patients integrate IC into their daily routines effectively [6,8]. However, the optimal method for educating patients remains undetermined, as educational practices vary widely across healthcare settings. There is currently no standardized approach to enhancing patient acceptance and adherence, underscoring the need for evidence-based educational strategies [2,4,7,9].

This protocol describes a multicenter, parallel-group, randomized controlled trial (RCT) designed to evaluate the effectiveness of an enhanced educational intervention for patients learning IC. The intervention consists of standard clinical training supplemented with an informational booklet and video tutorial to reinforce key concepts. The study will measure changes in IC acceptance using the Intermittent Catheterization Acceptance Test (I-CAT) alongside short-term adherence, urinary symptoms, functional autonomy, and patient satisfaction [10,11]. In other words, this protocol aims to provide a replicable methodology for improving IC training in clinical practice by standardizing and systematically evaluating this educational intervention. The results from this study may help to refine patient education strategies, ultimately improving adherence and patient-reported outcomes associated with IC [3,12].

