### Sampling procedure

The screening process will involve evaluating patients based on the predefined inclusion and exclusion criteria. This will include a review of medical records and an initial assessment to determine each patient’s eligibility for participation in the study. Once deemed eligible, patients will be approached consecutively and invited to participate. The recruitment process will continue until the required sample size is reached, ensuring that the study population is representative of the broader clinical population and diverse in terms of patient characteristics.

Before enrollment, written informed consent will be obtained from all participants. Patients will receive detailed information about the study, including its purpose, procedures, potential risks, and expected benefits. They will have the opportunity to ask questions before deciding whether to participate. Participation is entirely voluntary, and patients may withdraw from the study at any time without any impact on their standard medical care. After enrollment, participants will be assigned to one of the two study groups.

While contamination between groups is theoretically possible, it would likely lead to an underestimation of the intervention effect rather than an artificial inflation, as the intervention group receives all components provided to the control group plus additional materials. To mitigate this risk, participants were clearly instructed not to share training details or educational materials with others. Moreover, supplementary materials were distributed individually and not made publicly accessible, and educational sessions were scheduled to minimize overlap and patient interaction.

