### Sample size

The sample size for this study was determined to ensure sufficient statistical power to detect a meaningful difference in median I-CAT scores between the intervention and control groups. The primary endpoint aims to demonstrate an improvement in median I-CAT scores from 3.0 to 3.5, which corresponds to an increase from the median acceptance score to the 75th percentile of the previously reported distribution [10,11].

To achieve this, a significance level of 0.05 (5 %) was selected, meaning there is a 5 % probability of a Type I error, where a difference is incorrectly concluded when none exists. A power of 80 % (0.80) was chosen, ensuring that the study has an 80 % probability of detecting a true difference between the groups if one exists, thereby reducing the risk of a Type II error. Based on previous studies and pilot data, a standard deviation of 1 was assumed for the calculation [10,11]. Given these parameters, the sample size calculation was performed using a non-parametric (Mann-Whitney U) test to compare the two independent groups.

The formula used for calculating the required sample size accounts for effect size, significance level, and power. The required sample size per group, denoted as n, is calculated using the equation:(1)$$n=\frac{{\left(Z_{\alpha /2}+Z_{\beta }\right)}^{2}\times \;2\;\times \sigma^{2}}{\Delta^{2}}$$

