Self-report assessments will be administered to evaluate different aspects of the patient’s experience, adherence, and outcomes related to IC. All measurement tools selected for this study are supported by evidence of validity and reliability:(a)The Intermittent Catheterization Acceptance Test (I-CAT) will be administered at baseline (T0), one month post-initial training (T1), and three months post-initial training (T2). The I-CAT is designed to measure changes in acceptance rates of IC over time. It evaluates psychological comfort, willingness, and overall acceptance, helping to assess how well patients adapt to the procedure and the impact of educational interventions on their acceptance levels [10].(b)The Urinary Symptoms Questionnaire for Neurogenic Bladder in IC (USQNB-IC) will be conducted at T0, T1, and T2. This instrument evaluates urinary symptoms in patients with neurogenic bladder undergoing IC. It measures the severity and frequency of symptoms, including incontinence, urgency, and discomfort, allowing for the monitoring of symptomatic changes and potential improvements in urinary health with consistent IC use [14].(c)The Intermittent Catheter Adherence Scale (I-CAS) will be administered at T1 and T2 to measure adherence to the prescribed IC regimen. This tool assesses the frequency and consistency of catheter use as recommended by healthcare providers. Evaluating adherence through I-CAS will help identify barriers to consistent IC and assess the effectiveness of educational interventions in improving compliance [11].(d)The Autonomy Checklist will be completed at T0, T1, and T2 to assess procedural autonomy in IC. This checklist evaluates the patient’s ability to independently manage catheterization, including preparation, insertion, and hygiene maintenance. High scores indicate successful training and an increase in self-sufficiency in performing IC.(e)The Serendipity Questionnaire, developed by the researchers involved in this research, will be administered at T2 to capture subjective experiences and unexpected positive outcomes during the IC journey. This questionnaire includes items that explore patient insights, satisfaction, and any unexpected benefits they may have encountered. The qualitative data obtained will provide a richer understanding of the patient experience beyond clinical measures.(f)The Quebec User Evaluation of Satisfaction with Assistive Technology (QUEST) will be administered at T1 and T2 to assess patient satisfaction with the assistive devices used for IC. This instrument includes questions about the ease of use, effectiveness, and overall satisfaction with the catheter and related equipment. By identifying areas for improvement in device design and patient training, QUEST ensures that tools meet the practical needs of patients [15].(g)Motor function assessments will also be included in the study. The Motor Assessment using a Dynamometer will be conducted at T0 and T1 to measure grip strength, an essential factor in the ability to perform IC independently [16]. This test will help determine whether physical limitations may impact a patient’s ability to handle and use the catheter effectively by evaluating motor strength. The Manual Dexterity Assessment using the Nine Hole Test will be performed at T0 and T1 to measure fine motor skills, which are crucial for successful IC execution [17]. This test requires participants to place and remove pegs from a board, providing a quantitative measure of hand function. It will help identify patients who may require additional support or adaptive techniques to manage IC effectively.

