To further investigate factors associated with adherence and secondary outcomes, multivariable analyses will be performed. Logistic regression models will be used to analyze binary outcomes, such as adherence status, while linear regression models will be applied to continuous outcomes, including I-CAT scores. Predictor variables will include sociodemographic factors (e.g., age, education level, socioeconomic status), clinical characteristics (e.g., primary diagnosis, comorbidities), and intervention type (enhanced educational intervention vs. standard clinical training). Interaction terms will be incorporated to assess whether the effects of the intervention differ across subgroups, ensuring a comprehensive evaluation of potential effect modifiers. Model selection will be guided by theoretical considerations and statistical criteria, using stepwise or backward elimination methods to refine the models.

Handling missing data will be an important aspect of the analysis. This study assumes that data are missing at random (MAR), meaning that missingness is related to observed data but not to unobserved data [18]. All instances of missing data will be identified and documented, and patterns of missingness will be analyzed to determine whether they are systematically related to specific variables. Descriptive statistics will be used to summarize the extent and distribution of missing data for each variable.

Multiple imputation will be used as the primary method for handling missing data to minimize bias and preserve statistical power [19]. This approach generates multiple plausible datasets by imputing missing values based on observed data, which are then analyzed separately. The results from these datasets will be combined to produce estimates and confidence intervals that appropriately reflect the uncertainty introduced by missing data. Multiple imputations using chained equations will be performed, suitable for handling various variables, including continuous, binary, and categorical data.

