To evaluate the robustness of the findings, sensitivity analyses will be conducted, comparing the results of multiple imputations with alternative approaches, such as complete case analysis (where only participants with complete data are analyzed) and single imputation methods [18]. These analyses will ensure that the handling of missing data does not introduce bias into the study conclusions. The extent of missing data, the imputation methods applied, and the results of sensitivity analyses will be transparently reported in all study publications and presentations to ensure scientific integrity and reproducibility.

All statistical analyses will be performed using R (R Core Team, 2023). The significance level (alpha) for hypothesis testing will be set at 5 % (0.05). When multiple comparisons are conducted, appropriate adjustment procedures will be applied to control for Type I error inflation. Two-tailed tests will be employed for all analyses.

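### If men who reject catheterization miss visits unequally by arm, missing-at-random imputation can mask part of that rejection, and the named sensitivity analyses cannot rule this out

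*Protocol article*

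**What the plan says.** The protocol article's Statistical plan assumes that missingness depends on observed data only. It then states: "Multiple imputation will be used as the primary method for handling missing data to minimize bias and preserve statistical power". The method is chained equations, with values imputed from what was observed. No reason for missingness is treated differently from any other. The same section plans to study patterns of missingness. It gives complete case analysis and single imputation as examples of sensitivity analyses, and says that these will make sure missing-data handling does not bias the conclusions.

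The primary endpoint is the I-CAT acceptance score at T2, compared by Mann-Whitney. The I-CAT is taken at T0, T1 and T2. The I-CAS is "administered at T1 and T2 to measure adherence to the prescribed IC regimen" (Measurements). The Background lists discomfort, difficulty with the procedure and poor training, "all of which can negatively impact their acceptance and consistent use of IC". Under Sampling procedure, "patients may withdraw from the study at any time without any impact on their standard medical care".

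**The concern.** The trial measures whether men accept IC and keep to it. By the Background's own account, the forces that lower acceptance also lower use. A man who stops prescribed IC because he rejects it may therefore be more likely than others to leave T1 or T2 blank. If so, missingness depends on the unseen T2 score, and imputation under missing at random tends to place him too high.

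The arm that loses more such men is raised by more. If the booklet and video keep men on IC, part of the benefit is hidden. If they put men off, part of the harm is hidden. The primary I-CAT comparison and the adherence comparison are both exposed. The named checks would not reveal this, yet the article says that they settle the matter.

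**Working it through.** **Inputs from the protocol.** "a significance level of 0.05 (5 %) was selected"; "Two-tailed tests will be employed for all analyses"; "A power of 80 % (0.80) was chosen"; "improvement in median I-CAT scores from 3.0 to 3.5"; SD 1; 1:1 allocation; 64 per group.

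**The plan's own figure.** n = (1.96 + 0.84)² × 2 × 1² / 0.5² = 7.84 × 2 / 0.25 = 62.7, so 63 per group. The t-test version gives 63.8, so 64. At an effect of 0.2 the formula gives 7.84 × 2 / 0.04 = 392. Both stated figures reproduce. The total is exactly 2 × 64 = 128, with no allowance for loss.

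**Assumptions.** The documents give no loss rates, correlations between visits or reasons for loss. All of these are assumed below.

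**Check 1: bias in the difference.** T2 I-CAT is normal with SD 1 and means 3.0 and 3.5; the T1–T2 correlation is 0.5. Imputation is by regression on T1 within arm. The true difference is 0.50.

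| Loss, A / controls | What drives loss | Complete case | Imputation |
|---|---|---|---|
| 15% / 15% | low T2 score | 0.50 | 0.50 |
| 10% / 20% | low T2 score | 0.35–0.39 | 0.37–0.41 |
| 20% / 10% | low T2 score | 0.61–0.65 | 0.59–0.63 |
| 10% / 20% | low T1 score | 0.42 | 0.50 |
| 20% / 10% | low T1 score | 0.58 | 0.50 |

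- In the control arm with 20% loss driven by T2, the lost men's true mean is 1.6–2.0. Imputation gives them about 3.0–3.1, and completers average 3.25–3.35. With a correlation of 0.7 the imputed mean falls to about 2.7.
- When T1 drives the loss, imputed and true means agree (2.30 and 2.30). If T1 is left out of the imputation model, the last two rows become 0.42 and 0.58.
- When T2 drives the loss, complete case and imputation err together, so agreement between them is no reassurance.
- With no true effect, 64 per arm and unequal 10%/20% loss driven by T2, rejection is about 10–20% (600 runs, error about 2–3 points). Equal 15% loss driven by T2 gave 6–10%, so not all of the excess over 5% comes from the imbalance.

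**Check 2: rejection rate of the planned test.** Shift 0.5, SD 1, 64 per arm. Correlations among T0, T1 and T2 are 0.5, 0.4 and 0.6. Imputation uses arm, T0 and T1 (10 datasets). Loss is correlated 0.5 or 0.8 with T2 acceptance. Ranges span both strengths and independent repeats of the simulation.

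| Loss, A / controls | Imputation | Lost men ranked lowest |
|---|---|---|
| 5% / 15% | 66–69% | 79–84% |
| 15% / 5% | 85–92% | 38–51% |
| 10% / 10% | 77–84% | 61–70% |

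With no shift and 15% / 5% loss, imputation gives P(A > B) of 0.515–0.531 against 0.50, so the arm with more refusers looks slightly better. Ranking lost men lowest answers a composite question (score and persistence together). The gap between the columns is therefore not all bias.

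**Check 3: adherence.** Assume 80% of continuing men adhere in both arms, and 15% of controls and 5% of Group A stop and are not seen again. Counting stoppers as non-adherent gives 0.85 × 0.80 = 68% and 0.95 × 0.80 = 76%, a difference of 8 points. If imputation gives stoppers an adherence probability p, the arms become 0.68 + 0.15p and 0.76 + 0.05p, and the difference is 0.08 − 0.10p. At p = 0.80 (earlier data carry no information) it is 0; at p = 0.40 it is 4 points; at p = 0 it is the full 8.

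**The case against.** A reader might infer that men who give up IC drop out of the trial and are filled in with the scores of men who carry on, so that a known failure is overwritten and non-acceptance is erased. The documents do not support that.

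- No section ends follow-up when a man stops IC. The withdrawal sentence concerns leaving the study, the visits are scheduled for all, and the analysis is by intention to treat. A man who has stopped can still complete both scales and score low.
- His status is not known unless someone records it, and nothing says that a recorded outcome would be replaced.
- Imputation uses observed data. If T0 and T1 I-CAT and T1 I-CAS enter the model, a low T1 score pulls the imputed value down, and loss fully explained by T1 causes no bias.
- A man may stop because of dexterity or difficulty without rejecting IC.
- Equal loss leaves the between-arm difference close to the truth. The unequal rates above are invented.
- Imputation variables and further sensitivity analyses are often left to an analysis plan, which is not shown, and the list of sensitivity analyses is open-ended.

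All of this stands, and it limits the point. For the I-CAT, this is a missing-not-at-random question and not a separate kind of error. Two things remain. The article claims a guarantee that the analyses it names cannot give. A worst-value single imputation would test the assumption, but no such method is named. And because the intervention aims to improve acceptance and adherence, unequal outcome-driven loss is foreseeable.

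**Conclusion.** The point holds in limited form. The stated rule and its named checks cannot exclude bias from outcome-driven loss. Such loss biases the between-arm comparison if men who reject IC miss visits more often, this differs by arm, and their T0 and T1 data do not fully show it. Under assumed 10%/20% loss, the error is about 0.09 to 0.13 points on a true 0.50 (0.50 − 0.41 and 0.50 − 0.37), in either direction. Under assumed 5%/15% loss, the rejection rate moves to about 66–69% or 85–92%, depending on which arm loses more. Masking is partial. The full disappearance of the 8-point adherence difference is a limiting case that needs uninformative earlier data. The primary analysis need not be replaced.

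**What to change.** 1. State that T1 and T2 assessment, including the I-CAT, continues whether or not the man still performs IC. Record at each visit whether he does and, if not, whether he stopped against the prescription or no longer needs it.
2. In the adherence analysis, count men recorded as having stopped prescribed IC as non-adherent instead of imputing them.
3. Name T0 and T1 I-CAT and T1 I-CAS in the imputation model. Beside the primary analysis, prespecify a missing-not-at-random sensitivity analysis of T2 I-CAT: lowest rank for recorded stoppers without a score, which the Mann-Whitney test takes directly, or a delta or tipping-point analysis. Keep multiple imputation for other missing values.
4. Delete the statement that the present sensitivity analyses make sure there is no bias.

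The cost is a status item on the T1 and T2 forms and a paragraph of text. The lowest-rank analysis has less power when stopping is equal in both arms (about 61–70% against 77–84% at 10% each), so it belongs beside the primary analysis and not in its place.

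### The missing-data comparisons are said to ensure absence of bias, but agreement among the methods named cannot exclude bias if missing T2 scores depend on unseen acceptance

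*Protocol article*

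**What the plan says.** All the relevant text is in the Statistical plan of the protocol article.

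- Assumption: "This study assumes that data are missing at random (MAR), meaning that missingness is related to observed data but not to unobserved data".
- Primary method: "Multiple imputation will be used as the primary method for handling missing data to minimize bias and preserve statistical power", by chained equations, from the observed data.
- Diagnostic: "patterns of missingness will be analyzed to determine whether they are systematically related to specific variables".
- Sensitivity analyses: the imputation results are set against "alternative approaches, such as complete case analysis (where only participants with complete data are analyzed) and single imputation methods".
- Assurance: "These analyses will ensure that the handling of missing data does not introduce bias into the study conclusions".

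The text names no analysis in which missing scores are allowed to differ systematically from what the observed data predict. The Limitations section does not mention missing data or attrition, so nothing there qualifies the assurance.

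**The concern.** The assurance is a positive statement about what the comparison can deliver, and the comparison cannot deliver it. Whether MAR holds turns on values that were not observed. An analysis that keeps MAR, or replaces it with something stricter, says nothing about what happens when MAR fails.

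The issue is relevant to this outcome. The primary endpoint is acceptance of catheterization three months after training, the trial is open-label, and I-CAT is self-reported. The Background notes: "Many patients struggle with psychological discomfort, procedural difficulties, and inadequate training". A patient who has come to reject the procedure could plausibly not return the T2 questionnaire, and this could happen more often in one arm. MAR imputation would then give that patient the score expected of patients who stayed and had the same observed history, which may be too high.

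The stake is interpretation. If the three methods agree, the text as it stands would support a statement that missing data caused no bias, when the agreement shows only that the result is not sensitive to the choice among these methods.

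**Working it through.** **1. What each named component assumes**

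- Multiple imputation: MAR given the variables in the imputation model.
- Complete-case analysis of a two-group comparison: generally an assumption at least as strong as MAR, because it ignores observed predictors of dropout.
- Single imputation: no variant is specified. A regression-type variant uses the same observed data as multiple imputation and understates the variance. A worst-value variant would depart from MAR, but none is described.
- Check of missingness patterns: observed variables only, so it cannot distinguish MAR from missing not at random (MNAR).

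**2. Yardstick from the protocol**

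The Sample size section uses a difference of 0.5, SD 1, two-sided alpha 0.05 and 80% power. Its formula gives 2 × (1.96 + 0.84)² × 1² / 0.5² = 62.72, so 63 per group. The t-test version gives 63.8, so 64. The stated 64 per group reproduces and is not in dispute. The values 0.5 and 1 serve below as the scale for bias.

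**3. Arithmetic for the bias (assumed inputs)**

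Let m be the fraction missing in an arm, and d the amount by which the true mean of the missing patients lies below the MAR prediction. MAR imputation then overstates that arm's mean by m × d, so

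bias in (A − B) = m_A × d_A − m_B × d_B.

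- 10% missing in A, 20% in B, d = 0.5 in both: 0.05 − 0.10 = −0.05.
- The same with d = 1.0: 0.10 − 0.20 = −0.10.
- 15% missing in each arm, d = 1.0 in A only: 0.15 − 0 = +0.15. With the departure in B only: −0.15.

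These are 10%, 20% and 30% of 0.5. The first two work against the intervention. The third favours it or works against it, depending on the arm. The missing rates and departures are not in the documents.

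**4. Does agreement among the methods reveal the bias?**

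This was simulated with 64 per arm and 2,000 trials per scenario. Assumptions not in the documents: normal scores with SD 1, T0-to-T2 correlation 0.5, about 22% missing overall, and an imputation model with T0 score and arm but no T1 data. Single imputation was of the regression type. Entries are mean estimated differences (A − B).

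| Who is lost | True difference | Multiple imputation | Single imputation | Complete case |
|---|---|---|---|---|
| Low T2 scorers in A (MNAR) | 0 | 0.16 | 0.16 | 0.21 |
| Low T2 scorers in A (MNAR) | 0.5 | 0.66 | 0.66 | 0.70 |
| Low T2 scorers in B (MNAR) | 0.5 | 0.34 | 0.34 | 0.30 |
| Low T0 scorers in A (MAR) | 0.5 | 0.50 | 0.50 | 0.60 |

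In the three MNAR rows the methods lie within about 0.05 of each other, yet all are wrong by about 0.16 to 0.21. In the first row the complete-case Mann-Whitney test rejects in about 17% of trials instead of 5%. In the MAR row multiple imputation is right and complete case is off by 0.10, so the methods disagree although MAR holds. Agreement does not show absence of bias, and disagreement does not show that MAR fails.

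**The case against.** Several counter-arguments have force.

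- **The list is open, and a fuller plan may exist.** The alternatives are introduced as examples, and a condensed article may leave an MNAR analysis to a document not shown. A reader might infer that the trial has no such analysis. The article does not support that, and its silence is not the fault raised here. The fault is the printed assurance, which a longer list would not make true.
- **The text does not claim to test MAR.** It labels MAR openly as an assumption and gives robustness as the aim. Read as a check on the choice of method, the comparison is reasonable. The assurance, however, extends to the study conclusions.
- **Single imputation need not rest on MAR.** This is correct: worst-value or carry-forward rules rest on other assumptions. It would be too strong to say that no named method could depart from MAR. What stands is that no departure is described.
- **The protocol collects data that make MAR more credible.** According to Measurements, I-CAT is taken at T0, T1 and T2, and I-CAS at T1 and T2. Rejection visible at T1 becomes observed information. The simulation omits T1, so its residual bias may exceed what the trial's own data would give.
- **Difficulty with catheterization is not loss to follow-up.** The Background sentence gives no evidence about who will miss T2. It makes acceptance-related missingness plausible and no more.
- **Results will be reported openly.** The plan commits to reporting the extent of missing data, the imputation methods and the sensitivity results. That helps readers but does not correct the sentence.

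**Conclusion.** The assurance is wrong as written and should be changed. Comparing MAR-based imputation with complete-case analysis and an unspecified single imputation cannot ensure that missing data leave the conclusions unbiased.

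A reader might go further and infer that the primary result will be biased, or by a known amount or in a known direction. The documents do not support that, because they give no expected missing rate and no information on the mechanism. The shifts of about 0.05 to 0.15 points in either direction rest wholly on assumed rates and departures. They are also on the mean scale, whereas the primary endpoint is framed as a median and tested by Mann-Whitney U, so their ratio to the 0.5-point target is approximate. No stated figure, test or sample size changes.

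**What to change.** 1. Replace the assurance with: *These analyses will assess how far the conclusions depend on the missing-data assumptions.*
2. Add a delta-adjusted (tipping-point) multiple imputation of T2 I-CAT to the sensitivity analyses. Shift the imputed scores in both arms together and in each arm alone, over a range fixed in advance (for example up to 1 point, the assumed SD), and report the shift at which the conclusion changes.
3. State that the imputation model for T2 I-CAT includes T0 and T1 I-CAT and T1 I-CAS.
4. Complete-case analysis and single imputation may stay as secondary checks.

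The cost is one sentence of rewording and a little more analysis code. No extra data or patients are needed. The range of shifts should be fixed before outcome data are seen. If a fuller plan already contains such an analysis, only the wording needs to change.
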